### **Sample size justification**

The proposed sample size is based on having sufficient power for detecting treatment differences for primary and secondary outcomes. Regarding the percent of participants negative for illicit opioids at the 24-week assessment, power is estimated to be greater than 95% using  $\alpha=.05$  if true abstinence rates are as low as 60% vs. 15% for IBT and WLC groups, respectively. These estimates are more conservative than on our R34 outcomes, with lower abstinence predicted in IBT as we increase the duration to 24 weeks and move beyond a single research clinic for this Stage II trial. For secondary aims, effect sizes range from small to moderate. The estimated differences between conditions in mean change from baseline to 24 weeks corresponding to power=80% for representative ASI subscales are: Employment=.084 (ES=0.23), Psych=.076 (ES=0.36), Legal=.044 (ES=0.32), and Drug=.056 (ES=0.51). Similarly, power is 80% for detecting a mean difference of 4 units in the 24-week change in BDI (ES=0.30) which is smaller than we observed in our pilot trial. Lastly, power is estimated to be 80% to detect a mean absolute difference of 6% in the pre-post change in HIV knowledge scores (ES=0.39) and 5.5% (ES=0.34) for the pre-post change in OD knowledge scores. It should be noted that these ES's (Cohen d's) are expressed relative to the between-subject variability at baseline [i.e.  $(\Delta_{IBT}-\Delta_{WLC})/\sigma_{\text{between-subject}}$ ], not the variability in the change scores [i.e.  $(\Delta_{IBT}-\Delta_{WLC})/\sigma_{\Delta}$ ] (Becker, 1988; Morris, 2008). The actual computation accounts for the correlation observed across assessments for each outcome observed in our pilot data which is responsible for the different estimates of detectable ES's.

### **Health economic evaluation**

To determine the cost of each condition, we will employ the Brief Drug Abuse Treatment Cost Analysis Program (Brief DATCAP; French et al., 2004), a measure widely used in the area of substance abuse (e.g., French et al., 2008; Roebuck et al., 2003, 2009, 2011; <http://datcap.com/>). The economic cost of treatment will be derived by allocating fixed costs based upon the proportion of time or space utilized by the programs and costs that vary by patient engagement (e.g., urinalysis, medication). Total cost per treatment episode will be individual-specific and also include the opportunity cost of patient's time as measured by the Client (Outpatient) DATCAP (French, 2005; Salomé et al., 2003). The time period of cost analyses will span from intake to participants' discontinuation or trial completion. Cost of research-specific resources will be excluded. Costs and benefits will be expressed in constant prices. Estimated treatment costs will be combined with the estimated participant healthcare utilization costs to represent total costs per treatment condition. We will conduct benefit-cost (BC) and cost-effectiveness (CE) analyses from the societal perspective (Drummond et al., 2015). Based upon illicit opioid abstinence from Day 1 through the 24-week assessment, the number of quality-adjusted life years (QALYs) gained -as measured by the proportion of time spent in 'abstinent' or 'non-abstinent' status- will be derived (Cromwell et al., 1997; Flack et al., 2007; Zeckhauser & Shepard, 1976). BC and CE ratios will be computed by dividing the mean difference in treatment costs between the two conditions into mean difference in economic benefits or QALYs, respectively. Statistical significance of the ratios will be determined by employing non-parametric bootstrapped standard errors (Drummond et al., 2015). We hypothesize that,

while IBT costs will exceed that of WLC, they will be more than offset by the benefits realized (e.g., reduced health care and criminal justice costs, work days lost, QALYs).

**Risks/Benefits:** Describe any potential or known risks. This includes physical, psychological, social, legal or other risks. Estimate the probability that given risk may occur, its severity and potential reversibility. If the study involves a placebo or washout period, the risks related to these must be addressed in both the protocol and consent. Describe the planned procedures for protecting against or minimizing potential risks and assess their likely effectiveness. Where appropriate, discuss plans for ensuring necessary medical or professional intervention in the event of adverse effects to the subjects. Discuss the potential benefits of the research to the subjects and others. Discuss why the risks to the subjects are reasonable in relation to the anticipated benefits to subjects and others. Discuss the importance of the knowledge gained or to be gained as a result of the proposed research and why the risks are reasonable in relation to the knowledge that reasonably may result. If there are no benefits state so.

Risks include breach of confidentiality and any side effects associated with the study medication (i.e., buprenorphine). Breach of confidentiality: Study data include medical and psychiatric histories and biological measures of alcohol and illicit drug use and pregnancy. The likelihood of a breach of confidentiality is low as we will take precautions to minimize this risk as described below under Adequacy of Protection against Risk.

Side effects of buprenorphine: The side effects of buprenorphine include light-headedness, dizziness, sedation, lethargy, changes in sexual ability, nausea, vomiting, sweating, euphoria, constipation, respiratory depression, flushing of the face, skin itchiness or redness, darkening of the skin and/or swelling, bradycardia, headache, yawning, tearing, runny nose, muscle tremor, dilated or constricted pupil, restlessness, diarrhea, hypertension, hypotension, or potentially elevated liver enzyme levels (particularly among subjects with a history of hepatitis). The administration of the partial opioid agonist, buprenorphine, in individuals physically dependent on opioids should not result in acute toxicity because these individuals are tolerant to such drug effects. There also is a ceiling on the agonist effects of partial agonists; thus, the agonist effects of the partial agonist, buprenorphine, are considered to be safer than full agonists. Because buprenorphine is a partial agonist, it could also function as an antagonist and promote withdrawal symptomatology. We will administer buprenorphine in accordance with standard practice (see Methods) and, based on our previous experience in treating opioid-dependent individuals with this medication ([name] et al., 2009; [name] et al., 2013, 2015, 2016), we do not anticipate that buprenorphine-precipitated withdrawal or sedation will pose a problem.

Protection Against Risk: (1) To protect confidentiality, the guidelines stated in Title 42 of the Code of Federal Regulations, Part 2, "Confidentiality of Alcohol and Drug Abuse Records" will be followed. As stated in these regulations, subjects will be given a notice of federal confidentiality requirements (which will be included in the consent form). All records will be locked in file cabinets kept on site behind locked doors. Except for intake material, subjects' names (i.e., first and last names) will not be attached to the data forms. A central code/data base linking subject number with subject names will be kept, which will be available only to specified staff.

(2) In order to protect participants from any adverse effects of buprenorphine, a number of safeguards will be in place. First and most generally, subjects will be screened thoroughly at intake using medical, psychiatric, drug abuse, and cognitive interviews and self-reports. They will have a physical exam and follow-up interviews and tests may be ordered to clarify results. The results of all tests will be reviewed by the medical director ([name]) and the PI ([name]). Thus, we will document that the patient is healthy to participate in the proposed study. To prevent subjects who may have an insufficient level of opioid dependence from participating in these studies, they will have to meet several criteria (e.g., DSM-5 criteria for opioid dependence and FDA qualification criteria for buprenorphine treatment, including a history of opioid dependence and significant current opioid use). All medication administration will occur during working hours at the University Health Center (UHC), an inpatient/outpatient facility of the University of Vermont College of Medicine and University of Vermont Medical Center. All nursing and research staff will be trained by medical staff in detecting adverse effects. If a subject has any untoward effects, the Study Physician and PI will be contacted. Study Physician [name] will be on-call continuously for advice and assistance in the event that adverse effects occur. [name] has been working with our previous buprenorphine projects over the last 15 years, is a buprenorphine provider, is Medical Director of the Chittenden Clinic methadone program, and he has extensive experience with the clinical use of buprenorphine as a Vermont buprenorphine provider and trainer. The emergency room for the University of Vermont Medical Center is located approximately one block away from the UHC.

(3) Finally, patients are free not to participate in this study or to withdraw from it at any time. If they decide not to participate in the study, we will be glad to discuss with them other treatments that may be available in Vermont, including residential, outpatient, and medication-assisted treatment options. If

patients decide not to participate in this study or to withdraw from this study, their decision will not prejudice their future medical care at the University of Vermont or University of Vermont Medical Center. The investigators also retain the right to terminate patients' participation in the study if in their judgment continued participation would put them in physical or psychological danger. Additional details on our data and safety monitoring of the proposed research to ensure the safety of subjects is provided in the below section entitled "Data and Safety Monitoring Plan".

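### Trial 2's cost-effectiveness ratio uses treatment costs only, so it does not meet the societal perspective the plan claims for it

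*Supplement*

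**What the plan says.** All of this stands in the Trial 2 protocol, Health economic evaluation. The list of changes after Trial 2 began does not amend it.

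- **Treatment cost.** "The economic cost of treatment will be derived by allocating fixed costs based upon the proportion of time or space utilized by the programs", together with costs that vary with engagement, such as urinalysis and medication. Patient time is added: "Total cost per treatment episode will be individual-specific and also include the opportunity cost of patient's time".
- **A wider total.** "Estimated treatment costs will be combined with the estimated participant healthcare utilization costs to represent total costs per treatment condition".
- **Perspective.** "We will conduct benefit-cost (BC) and cost-effectiveness (CE) analyses from the societal perspective".
- **The ratios.** "BC and CE ratios will be computed by dividing the mean difference in treatment costs between the two conditions into mean difference in economic benefits"; for CE, the QALY difference replaces benefits over the same cost term.
- **Expected result.** IBT is expected to cost more than the waitlist control, with the extra cost "more than offset by the benefits realized (e.g., reduced health care and criminal justice costs, work days lost, QALYs". This is the only place where the benefits are itemised.

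**The concern.** The section defines a narrow cost quantity and a wider one, claims a societal perspective for both analyses, and then names only the narrow quantity in both ratios. For BC that is workable, because downstream savings can sit among the benefits. For CE it is not. The effect side is QALYs alone, so a saving in health care, criminal justice or work days has nowhere to enter except the cost term, and the cost term excludes it.

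As written, the CE cost term cannot respond to downstream offsets, however large they are. Yet the economic hypothesis is largely about such offsets. A published figure labelled societal would not have that property. An analyst who noticed the gap could also choose the cost definition after seeing the data.

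**Working it through.** The plan gives no cost, benefit, QALY or ratio figure, so there is no stated result to reproduce. The check sets the definitions side by side and then works through the algebra with assumed amounts.

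**Step 1. What each quantity contains.** The first two columns follow the plan's definitions. The third holds every consequence that the section itself names, apart from QALYs.

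| Component | Treatment costs | Total costs | Societal, as claimed |
|---|---|---|---|
| Programme resources | yes | yes | yes |
| Patient time | yes | yes | yes |
| Health care utilization | no | yes | yes |
| Criminal justice | no | no | yes |
| Work loss | no | no | yes |
| Named in the CE ratio | yes | no | no |

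Putting total costs into the CE ratio would therefore close only part of the gap.

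**Step 2. Formulas.** Let T be the extra treatment cost of IBT, H the health care savings, O the criminal justice and work-loss savings, and dQ the QALY difference.

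- CE as literally worded: dQ / T, which is QALYs per dollar. Its reciprocal is T / dQ.
- CE from the stated perspective: (T - H - O) / dQ.
- Written cost per QALY relative to societal cost per QALY: T / (T - H - O). The QALY difference cancels, so no assumption about it is needed.

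**Step 3. Size, with assumed amounts (T = 100).**

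| H | O | Cost term as written, T | With health care, T - H | Societal, T - H - O | T / (T - H - O) |
|---|---|---|---|---|---|
| 10 | 25 | 100 | 90 | 65 | 1.54 |
| 10 | 75 | 100 | 90 | 15 | 6.67 |
| 25 | 25 | 100 | 75 | 50 | 2.00 |
| 25 | 75 | 100 | 75 | 0 | undefined |
| 50 | 25 | 100 | 50 | 25 | 4.00 |
| 50 | 75 | 100 | 50 | -25 | sign differs |
| 75 | 25 | 100 | 25 | 0 | undefined |
| 75 | 75 | 100 | 25 | -50 | sign differs |

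**Step 4. When the sign differs.** With T positive, T - H - O is below zero exactly when H + O exceeds T, that is, when the monetary offsets alone exceed the extra treatment cost. The plan's hypothesis is weaker than that, because QALYs are among its offsetting benefits. Take an assumed extra cost of 2,000, monetary savings of 1,500 and QALYs valued at 1,000. Benefits are 1,500 + 1,000 = 2,500, above 2,000, so the hypothesis holds. The societal cost difference is 2,000 - 1,500 = +500, still positive.

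**Step 5. The BC ratio.** As worded it is (H + O) / T, with health care savings counted once, in the numerator. If total costs were put in the denominator it would become (H + O) / (T - H), larger by the factor T / (T - H). With T = 100, H = 50 and O = 25, that is 75/100 = 0.75 against 75/50 = 1.50.

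**The case against.** Much of the case on the other side stands.

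- **Double counting in BC.** A reader might infer that the shared cost term makes BC count health care savings twice. The documents do not support this. Treatment costs and total costs are defined separately, the ratio sentence uses the former, and the hypothesis places health care savings among the benefits. Double counting needs a different term from the one written.
- **Dominance.** A reader might also infer that the hypothesis implies a negative societal cost difference, so that the CE cost term must have the wrong sign if the hypothesis is true. Step 4 shows otherwise.
- **Concealment.** BC is reported beside CE, and (H + O) / T exceeds 1 exactly when T - H - O is below zero. A net saving would then be visible in BC, provided its benefits are monetary savings only. If valued QALYs are included, BC above 1 no longer shows this: in the Step 4 example it is 2,500/2,000 = 1.25 with a net cost of 500.
- **Scope of the cost term.** It includes patient time, so calling it a pure programme cost would be wrong.
- **Total costs.** They can be reported for each condition in their own right. The text shows only that neither ratio names them.
- **Direction of the ratio.** QALYs per dollar is the reciprocal of cost per QALY and loses no information.

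None of this puts health care, criminal justice or work loss into the CE ratio. The mismatch between the claimed perspective and the CE cost term remains.

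**Conclusion.** The point holds for the CE ratio only: as worded it is partly societal, whatever the data turn out to be. In the illustrations, the written cost per QALY is 1.54 to 6.67 times the societal figure where the societal cost difference is positive. The two cost terms have opposite signs once monetary offsets alone exceed the extra treatment cost.

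This rests on three assumptions. Treatment costs mean what the section defines them to mean. IBT costs more to deliver than the waitlist control, as the plan expects. The consequences itemised in the hypothesis, given there as examples, are ones that a societal analysis here should carry. The amounts are invented for illustration and say nothing about this trial's results.

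The primary abstinence outcome and its test are untouched. The matter deserves correction because the repair is specific and cheap.

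**What to change.** Write out each ratio's cost term separately.

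- **CE.** Use the difference in net societal costs: treatment including patient time, plus health care, criminal justice and work loss, each counted once. If narrower costs are intended, name that perspective in place of societal. State the ratio as cost per QALY.
- **BC.** Keep treatment costs in the denominator and health care savings in the benefits only. Say so explicitly, so that total costs are not substituted later and health care savings counted twice. State whether valued QALYs belong to the benefits.
- **Uncertainty.** The plan bootstraps standard errors for the ratios. The societal cost difference may be near zero or negative, where a cost-per-QALY ratio is hard to interpret. Bootstrap the incremental net monetary benefit instead: the value placed on a QALY times the QALY difference, minus the societal cost difference, over a stated range of QALY values.

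The cost is a few sentences in the section and a little more analysis, using components that the plan already names.

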#### Potential Benefits to Participants and Others

Volunteers may benefit by initiating abstinence from illicit opioids during their study participation, including experiencing a reduction in the wide range of medical, financial, psychosocial, and legal consequences associated with illicit opioid abuse. Volunteers may also benefit from the financial compensation provided as part of the proposed study. By improving treatment access for opioid abuse and dependence, the proposed research also stands to benefit public health in general by reducing the vast economic and societal costs associated with opioid abuse (e.g., health service utilization and costs, criminal activity, contraction of preventable diseases such as HIV and hepatitis). In addition, there are potential scientific benefits to be gained by expanding our empirical knowledge on how to mitigate gaps in treatment access among opioid-dependent individuals. Overall, the individual participant, the medical and scientific communities, and society in general may benefit by our efforts to develop an interim buprenorphine treatment for patients awaiting agonist maintenance. As such, the risks to which individuals may be exposed as a function of their research participation are reasonable in relation to the anticipated benefits.

#### Importance of the Knowledge to be Gained

The proposed project has the potential to contribute a novel and effective technology-assisted pharmacotherapy protocol that can be widely disseminated to bridge gaps in access to life-saving opioid treatment. Thus, knowledge gained from this research may significantly enhance the accessibility, implementation and effectiveness of drug abuse treatment more generally. Consequently, the risk/benefit ratio is favorable. The risks to which individuals are exposed as a consequence of their research participation are generally less than that associated with continuing their ongoing abuse of illicit opioids. In contrast, the potential and probable benefits to be derived by society in general and by opioid abusers as a group are considerable. In summary, conducting this research seems well justified.

**Therapeutic Alternatives:** *List the therapeutic alternatives that are reasonably available that may be of benefit to the potential subject and include in the consent form as well.*

#### ☐ **Not Applicable**

Participants are free not to participate in this study or to withdraw from it at any time. If they decide not to participate in the study, we will be glad to discuss with them other treatments that may be available in Vermont, including residential, outpatient, and medication-assisted treatment options.

**Data Safety and Monitoring:** *The specific design of a Data and Safety Monitoring Plan (DSMP) for a protocol may vary extensively depending on the potential risks, size, and complexity of the research study. For a minimal risk study, a DSMP could be as simple as a description of the Principal Investigator's plan for monitoring the data and performance of safety reviews or it could be as complex as the initiation of an external, independent Data Safety and Monitoring Board (DSMB). The UVM/UVM Medical Center process for review of adverse events should be included in the DSMP.*

**Patient eligibility and status.** All intake data collection will be conducted by a trained bachelor's-level Research Assistant (RA) using specialized forms and procedures. Medical screening data will be reviewed by the Study Physician. All intake information will be reviewed by the PI, who will determine participant eligibility. Only trained and IRB-approved research staff will complete informed consent with eligible and willing participants. The status of all active participants will be reviewed at weekly meetings between the PI, Co-investigators and RAs.

**Rigorous data management/Quality assurance.** The majority of study data collection will be conducted using self-report questionnaires. Randomly selected data will be checked by the RAs for completeness and to ensure quality (i.e., no appearance of rote answers, etc.). In terms of standard operating procedures at the clinic, all assessments will be administered by trained research staff. All subject data will be maintained in secure filing cabinets behind locked doors in order to protect confidential subject information. Safe places will include locked filing cabinets or locked rooms that will be accessible only to study personnel. Full subject names will not be listed on the outside of the binders in order to protect the identity of study participants. Moreover, all data that are entered into spreadsheets and databases, in preparation for data analyses, will be entered twice. That is, two separate individuals will enter the data into databases, and a comparison between data entries will be conducted to detect data entry errors. All discrepancies in data entry will be checked against the raw data source, and the correct data entry will be used. All data that are entered into spreadsheets and databases will be coded by subject

ID number and not by subject name. Additionally, all entered data will be backed up on an external hard drive or a secure project server at least weekly. The biostatistician and PI will discuss any problems at monthly data meetings. Additional meetings will be conducted on an as-needed basis. An original copy of the data will be retained at the clinic should anything happen to the document during transmission.

**Auditing procedures.** Review of any problems related to quality of data collection, transmission or analyses and of any AEs and SAEs that occurred during the past week will occur at weekly research staff meetings. Interim analyses of efficacy data will be conducted when half the subjects have been entered or at other times based on the joint discretion of the PI, Co-I and biostatistician.

**Adverse Event and Unanticipated Problem (UAP) Reporting:** Describe how events and UAPs will be evaluated and reported to the IRB. All protocols should specify that, in the absence of more stringent reporting requirements, the guidelines established in the Committees on Human Research "Adverse Event and Unanticipated Problems Reporting Policy" will be followed. The UVM/UVM Medical Center process for review of adverse events and UAPs to subjects or others should be included in the DSMP.

AEs and SAEs will be assessed at each clinic visit by a trained RA or nurse. Any SAE will be brought to the attention of the PI as soon as possible and not longer than 24 hrs. Any SAE, whether or not related to study intervention, will be reported to the IRB using the UVM Adverse Event Reporting Document within 5 days of the event. The IRB will make a determination as to whether additional reporting requirements are needed. Any SAEs will also be summarized in the yearly IRB continuing review, including a review of frequency and severity.

**Withdrawal Procedures:** Define the precise criteria for withdrawing subjects from the study. Include a description of study requirements for when a subject withdraws him or herself from the study (if applicable).

Completing study visits and providing urine specimens as scheduled are necessary in order for subjects to receive the study medication. Thus, if the subject fails to attend scheduled visits, or does not submit regularly scheduled urine specimens, or if there is any evidence of nonadherence to the medication regimen, they will be withdrawn from the study. If they are discharged from the study, subjects will be expected to return all remaining medication and the Med-O-Wheel device to study staff immediately. Females will be tested for pregnancy prior to and during the study. Should a subject become pregnant during the trial, her participation will be terminated and she will be assisted with accessing treatment at the medical center's high-risk pregnancy clinic. Patients are free not to participate in this study or to withdraw from it at any time. If they decide not to participate in the study, we will be glad to discuss with them other treatments that may be available in Vermont, including residential, outpatient, and medication-assisted treatment options. If patients decide not to participate or to withdraw from this study, their decision will not prejudice their future medical care at UVM or UVM Medical Center.

**Sources of Materials:** Identify sources of research material obtained from individually identifiable human subjects in the form of specimens, records or data. Indicate whether the material or data will be obtained specifically for research purposes or whether use will be made of existing specimens, records or data.

Research materials will include questionnaires, structured clinical interviews, expired air samples for analyzing breath alcohol levels, urine samples for analyzing recent drug use and pregnancy status. All data will be collected for research purposes only. All data collection will be conducted by a trained bachelor's-level Research Assistant (RA) with special training on all forms and procedures. All information will be reviewed by the PI, who will determine participant eligibility and complete informed consent with eligible and willing participants. Subject data will be maintained in secure filing cabinets behind locked doors in order to protect confidential subject information. Safe places will include locked filing cabinets or locked rooms that will be accessible only to study personnel. Full subject names will not be listed on the outside of the binders in order to protect the identity of study participants. Subject data and subject identifiers will only be accessible to approved research staff.

